### Outcome measures

2.4

#### Primary outcome measures

2.4.1

We will use the skin lesions score scale as the primary outcome indicator. This scoring table was developed in accordance with the guidelines of the latest version of the “Guidelines for Clinical Research of New Chinese Medicines.” This score sheet is an evaluation index for the main symptoms of acne, and comprehensively evaluates the main efficacy of each treatment plan. The scoring items of the scoring table are to evaluate the amount and distribution of skin lesions such as pimples, nodules, and cysts. There are 4 main items to be scored, namely the type of skin lesions, the number of skin lesions, the degree of swelling and rupture, and the color of the skin lesions. Each item is divided into 4 severity levels, which are rated as 0 points, 2 points, 4 points, and 6 points in turn, and the total score is finally calculated.

#### Secondary outcome measures

2.4.2

We will use the systemic symptom recording scale as the secondary outcome measure. This record scoring table is based on TCM-related symptoms of acne. It reflects the changes in the symptoms of acne patients after various treatments, and it is of auxiliary evaluation significance. Evaluation content includes complexion, emotion, urination, stool, sleep, appetite, menstruation (female patients only), etc. The score is divided into 2 levels, which is 0 for normal and 1 for abnormal. The above 2 scoring tables were evaluated every 2 weeks before and during the treatment, that is, a total of 3 evaluations. Observe the therapeutic effect of each treatment scheme on the condition of acne as a whole.

### Randomization and blinding

2.6

All 60 patients with acne vulgaris that met the research criteria will be divided into intervention group and control group, each with 33 cases. All patients included in this clinical observation will be given numbers from 1 to 60 according to the time of inclusion. Then abide by the idea of random method, the computer software generates 60 random numbers, and the 60 random numbers correspond to the patient number one by one. The random numbers assigned to the patients after the division are going to be divided by 2. If the random number is divisible, the patient will be assigned to the intervention group. If the random number is not divisible, it will be assigned to the control group (that is, the random number is incorporated into the experimental group and the odd number is incorporated into the control group). Until 1 group was full, the remaining patients were assigned to the other group.

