### Study design and settings

2.1

The study will be a randomized controlled trial divided into 2 parallel groups. This protocol is based on the Standard Protocol Project: Recommended Guidelines for Interventional Trials. If they agree, they will sign an informed consent form. Following the schedule described in Figure 1, only participants who read and agreed to the agreement and signed informed consent will be allowed to participate in the study. After patients were included in this clinical observation, the research guidelines of randomized controlled trials will be strictly followed, and the randomized number table method are going to be used to divide the admitted patients into test groups and control groups on average.

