#### Diagnostic criteria

2.2.1

The diagnostic criteria for western medicine used in this clinical research project are strictly in accordance with the relevant descriptions in the textbook “*Clinical Dermatology*” (editor: Zhao Zhan). The main points of diagnosis are as follows:

① The age of onset is young people, male, or female. The most prone areas are the cheeks and forehead, followed by some areas with strong sebum secretion, such as the front chest, back, and shoulders.② The lesions show skin-like changes, usually pimples, blackheads, acne, knots, nodules, cysts, and scars. These skin lesions are generally symmetrical in the affected area, and are usually accompanied by strong sebum secretion, a slow and persistent condition.

Acne Severity Grading Standards: The acne grading standards used in this clinical research project are derived from the grading standards established by Pillsbury. The classification criteria are as follows:

① Grade I (mild): most of the types of skin lesions are blackheads, which do not appear intensively or intermittently, and are accompanied by a small amount of inflammatory pimples.② Grade II (moderate): most of the types of skin lesions are acne. The lesions are mainly concentrated on the face, accompanied by a moderate number of pimples and acne that may develop further.③ Grade III (Severe): the type of skin lesions is mainly inflammatory pimples and acne. The main lesions are on the face, neck, chest, and back, with a small number of nodules (less than 3). The number is around 51 to 100.④ Grade IV (severe): the type of skin lesions is mainly inflammatory pimples that may develop further, accompanied by more nodules and cysts (greater than 3), the number of skin lesions is greater than 100, and the probability is greater scar.

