#### Exclusion criteria

2.2.3

Patients will be excluded if they meet the following criteria:

① The incidence of acne is classified as patients with nodular acne, agglomerated acne, scarring acne, fulminant acne, and premenstrual acne.② During the observation period of this clinical study, patients who are unavoidably exposed to direct sunlight or receive high-intensity ultraviolet rays are unavoidable.③ Acne caused by long-term exposure to specific chemicals or acne caused by long-term use of glucocorticoids.④ Those who are allergic or scarred, and patients who disagree with the treatment plan used in this clinical research.⑤ Patients with severe cardiovascular and cerebrovascular diseases, cardiopulmonary insufficiency, liver and kidney dysfunction, and severe infections;⑥ Women during pregnancy or lactation.

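### The allocation procedure has no concealment step, and its fill-until-full rule makes about the last 6 assignments certain to anyone counting the arms

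*Protocol article*

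**What the plan says.** Section 2.6 (Randomization and blinding) prints the procedure in steps.

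- Numbering: "All patients included in this clinical observation will be given numbers from 1 to 60 according to the time of inclusion".
- Sequence: "the computer software generates 60 random numbers, and the 60 random numbers correspond to the patient number one by one".
- Decoding: "If the random number is divisible, the patient will be assigned to the intervention group"; odd numbers go to control.
- Balancing: "Until 1 group was full, the remaining patients were assigned to the other group".

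Section 2.1 describes the source differently: "the randomized number table method are going to be used to divide the admitted patients into test groups and control groups on average". Neither section says who holds the list, how an assignment is released, or that recruiters are kept from seeing it.

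The surrounding design matters too. Section 2.2 recruits from an acupuncture clinic and a dermatology clinic between July 2020 and July 2021. Section 2.2.2 requires severity of grade II or above. In section 2.2.1 grade II is described as "accompanied by a moderate number of pimples and acne that may develop further", without a lesion count, whereas grades III and IV carry counts. The primary outcome (section 2.4.1) is a rater's score of lesion type, number, swelling and rupture, and colour. Section 2.4.2 has it taken before and during treatment, three times in all.

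**The concern.** A random sequence protects a trial only if the person deciding on entry cannot tell which arm comes next. Here the sequence is keyed to order of inclusion, a number's parity reveals its arm, and nothing in the text separates the list from the recruiter. The last stretch of recruitment is also predictable by rule.

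A recruiter who knows the next arm can defer or decline a patient, or read a borderline grade or baseline score differently. The arms then differ before treatment starts. Section 2.7 names t tests and one-way analysis of variance, with no baseline adjustment that might absorb part of the difference.

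**Working it through.** **1. Inputs.** Section 2.6 gives an even/odd rule and a fill rule. Arm sizes conflict: "All 60 patients with acne vulgaris that met the research criteria will be divided into intervention group and control group, each with 33 cases", yet 2 × 33 = 66, the total in section 2.5. Both consistent pairings are therefore shown: 60 patients with 30 per arm, and 66 with 33 per arm. Even and odd are taken as equally likely.

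**2. Before an arm is full.** Parities are independent and fair, so arm counts say nothing about the next assignment. Foreknowledge at this stage needs sight of the list.

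**3. After an arm is full.** Let m be the arm size. The first arm fills at patient m + j when the other arm holds j patients (j = 0, …, m − 1), leaving r = m − j forced assignments:

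P(r = m − j) = 2 × C(m + j − 1, m − 1) × 0.5^(m + j)

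The mean is E(r) = 2m × C(2m, m) / 2^(2m).

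| | 60 patients, m = 30 | 66 patients, m = 33 |
|---|---|---|
| Mean forced assignments | 6.2 | 6.5 |
| Share of all patients | 6.15/60 = 10.3% | 6.46/66 = 9.8% |
| Median; 90th percentile | 5; 12 | 6; 12 |
| P(5 or more) | 0.59 | 0.61 |
| P(10 or more) | 0.20 | 0.23 |

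Only one arm receives needles, so counting the arms is easy for clinic staff. Hiding the list does not hide these assignments.

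**4. What foreknowledge could do (assumptions, not trial facts).** Take 30 per arm, no true effect, and outcome y = 0.6z + 0.8e with z and e standard normal, so that y has SD 1. When the next slot is acupuncture, a recruiter passes over a patient in the worst-prognosis fraction p once and takes the next patient. The mean of z in that arm moves by φ(z_p), the normal density at the cut-off, so the bias is 0.6 × φ(z_p). The standard error of the difference is √(2/30) = 0.258. The false-positive rate is approximately Φ(−1.96 + b/0.258) + Φ(−1.96 − b/0.258), where b is the bias.

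| Behaviour | Bias b (SD) | b/0.258 | Two-sided false-positive rate |
|---|---|---|---|
| Worst 20%, half passed over | 0.5 × 0.6 × 0.280 = 0.084 | 0.33 | 0.051 + 0.011 = about 6% |
| Worst 20%, all passed over | 0.6 × 0.280 = 0.168 | 0.65 | 0.095 + 0.005 = about 10% |
| Worst 30%, all passed over | 0.6 × 0.348 = 0.209 | 0.81 | 0.125 + 0.003 = about 13% |

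Simulation of the same model agrees: 0.08 SD and about 6%; 0.16 to 0.17 SD and about 10%; 0.21 SD and about 13%. These scenarios suppose that every acupuncture slot is foreseeable, which requires access to the list. The forced tail alone exposes about a tenth of assignments.

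**The case against.** The strongest reply is that this is a condensed article. Who holds the list is the kind of detail left to the full protocol, and numbering patients in sequence is ordinary practice. That stands as far as access to the list goes: the text shows a gap, not a breach. It does not answer the fill rule, which is printed and predictable as written.

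Several stronger readings are tempting but not supported.

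- **Recruiters work from a list made in advance.** The text numbers patients and then generates random numbers. Generating them all after the last inclusion would hide the next arm. That sits badly with a year of recruitment and a sequential fill rule, but advance generation remains an inference.
- **This is alternation.** It is not; the parity belongs to a random number.
- **Baseline is scored after the arm is known.** The order is not stated in the text. It may appear in the schedule and flow-chart figures, which are not shown.
- **Bias must favour acupuncture.** Staff who believe in acupuncture might equally steer severe cases towards it. The uncounted grade I/II boundary affects the mildest patients, so it does not map onto the worst-prognosis scenario above. The exclusion of "patients who disagree with the treatment plan used in this clinical research" turns on the patient's view, not the recruiter's.
- **No analysis could repair it.** In the model used here, adjusting for z would remove the selection bias if z were the measured baseline score. It would not do so if selection used something unmeasured or if the baseline score itself were distorted.

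**Conclusion.** The point holds in this form: the printed procedure contains no concealment step, and its fill rule makes on average about 6 final assignments (about 10%) certain to anyone tracking arm counts. That figure rests only on the stated rule, fair parity and equal arms.

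The effect on the primary comparison is a risk of unknown direction. The range of 0.08 to 0.21 SD, with false-positive rates of about 6% to 13%, depends on an assumed correlation of 0.6 and on assumed recruiter behaviour. The upper end needs consistent subversion and should not be read as the expected result. The change should be made before recruitment, which section 2.9 says has not begun.

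**What to change.** Rewrite the allocation paragraph in section 2.6 so that:

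1. An existing staff member who does not recruit, treat or score generates and holds the list.
2. Computer-generated permuted blocks of varying size, not disclosed to recruiters, replace the parity and fill-until-full rule. Envelopes alone would leave the forced tail visible.
3. Each assignment is released by sequentially numbered, opaque, sealed envelope or by telephone, only after consent, confirmed eligibility and a signed, dated baseline skin lesion score.
4. The random number does not appear on any form the rater sees.

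The same paragraph should state one total, one arm size and one source of the sequence, because 60 versus 66, 30 versus 33, and number table versus software now conflict.

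The cost is one paragraph, a set of envelopes if that route is chosen, and a few minutes per enrolment.

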### Statistical analysis.

2.7

SPSS for windows 24.0 statistical analysis software will be used for calculation, and normality test and homogeneity test of variance will be performed on each group of data. For measurement data in which the data conforms to the normal distribution, we will use the mean ± standard deviation. For non-normally distributed measurement data, the median ± quartile interval is used. General data comparison between the 2 groups using independent sample *t* test. Comparisons before and after treatment will be performed using *t* test for paired data. One-way analysis of variance will be used for comparison between groups. X^2^ test will be used for count data, and nonparametric rank sum test will be used for rank data. All statistical tests are two-sided. *P* < .05 indicates a significant difference.

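### The between-arm comparison should be a baseline-adjusted ANCOVA and the only efficacy test; the paired before/after tests within each arm cannot show an effect of acupuncture

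*Protocol article*

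**What the plan says.** All quotes are from the protocol article.

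- **Design (2.1):** "The study will be a randomized controlled trial divided into 2 parallel groups". Under Interventions (2.3), the control arm uses a topical cream, and the intervention arm receives the same measures plus acupuncture.
- **Primary outcome (2.4.1):** "We will use the skin lesions score scale as the primary outcome indicator". Four items, each scored 0, 2, 4 or 6, are summed, so the total runs from 0 to 24.
- **Timing (2.4.2):** both scales are scored every two weeks, before and during treatment: "that is, a total of 3 evaluations". A pre-treatment lesion score is therefore collected.
- **Tests (2.7):** "General data comparison between the 2 groups using independent sample" t test, which reads as the comparison of baseline characteristics; "Comparisons before and after treatment will be performed using" a paired t test; and "One-way analysis of variance will be used for comparison between groups". The section adds "All statistical tests are two-sided" and that P "< .05 indicates a significant difference".

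Section 2.7 names no covariate. It does not say whether the ANOVA is of the final score or of the change, and it does not rank the between-arm test above the before/after tests.

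**The concern.** Two features of the stated method are weak.

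First, the between-arm test makes no covariate adjustment for the baseline lesion score. Section 2.5 describes the trial as small and gives no effect size, SD or power, so there is no sign that precision can be spared.

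Second, the paired tests compare each arm with itself. Improvement is to be expected in both arms because both use the cream. A significant before/after change in the acupuncture arm mixes the effect of the cream, the natural course of the acne and any effect of acupuncture. Section 2.7 nevertheless gives these tests the same P < .05 standing as the between-arm test. That leaves room for a claim based on one arm being significant and the other not, which is not a comparison of the arms.

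**Working it through.** **The plan's own figure.** The article gives no power, effect size or SD, so there is no stated power to reproduce. The effect sizes and correlations below are assumptions and are shown as ranges.

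**Inputs.**
- Two arms, two-sided alpha 0.05 (2.1, 2.7).
- Patients per arm: 66 in total with up to 20% drop-out (2.5) leaves 66 × 0.8 = 52.8, about 26 per arm. The article also gives 60 in total and 30 or 33 per arm, so 30 per arm is shown as a check.
- Assumed: a between-arm difference d of 0.6 SD of the final score, and a baseline-to-final correlation ρ of 0.3, 0.5 or 0.7.

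**Step 1: one-way ANOVA with two arms.** Here F = t². In a simulated example with 30 per arm, t = 1.917 and F = 3.674, and both give P = 0.0602.

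**Step 2: power of the between-arm test.** Residual SD, relative to the SD of the final score:
- final-score ANOVA: 1
- change-score ANOVA: √(2(1−ρ)) = 1.183, 1.000, 0.775 at ρ = 0.3, 0.5, 0.7
- ANCOVA: √(1−ρ²) = 0.954, 0.866, 0.714

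Power comes from the noncentral t distribution with noncentrality (d / residual SD) × √(n/2).

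| n = 26 per arm, d = 0.6 | ρ = 0.3 | ρ = 0.5 | ρ = 0.7 |
|---|---|---|---|
| Final-score ANOVA | 56% | 56% | 56% |
| Change-score ANOVA | 43% | 56% | 78% |
| ANCOVA | 60% | 69% | 84% |

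At ρ = 0 ANCOVA gains nothing over the final-score ANOVA. With n = 26 and d = 0.5, the final-score ANOVA has 42%, and ANCOVA 46%, 53% and 70%. With n = 30 and d = 0.5, the figures are 48%, and 51%, 59% and 76%.

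**Step 3: validity.** In 20,000 simulated trials with no arm difference (30 per arm, ρ = 0.5), the type I error was 4.9% for the final-score ANOVA and 4.8% for ANCOVA.

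**Step 4: the paired tests when acupuncture adds nothing.** Let both arms truly improve by δ, in units of the SD of the change. Each paired test has power p, with noncentrality δ√26 and 25 degrees of freedom. The two tests disagree with probability 2p(1−p).

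| δ | p | Disagree: 2p(1−p) | Both significant: p² |
|---|---|---|---|
| 0.2 | 0.165 | 28% | 3% |
| 0.35 | 0.404 | 48% | 16% |
| 0.5 | 0.688 | 43% | 47% |
| 0.8 | 0.975 | 5% | 95% |

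Disagreement cannot exceed 50%, its value at p = 0.5, so 48% is close to the worst case. With a large improvement the tests agree, but only because both are significant, which again does not separate the arms.

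**The case against.** The strongest reply is that Section 2.7 already contains a valid between-arm test and that choosing ANCOVA is a matter of efficiency. That stands. The ANOVA holds its error rate, and what is lost is precision. The gain depends on a correlation the article does not give: it is nil at zero and about 4 points at 0.3.

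Three stronger readings are tempting, and the article does not support them.

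- **That the ANOVA discards the baseline score.** The article does not say whether the final score or the change is analysed, and a change-score ANOVA does use the baseline. At a correlation of 0.7 that narrows ANCOVA's advantage from 28 points (84% against 56%) to 6 (84% against 78%). At 0.3 the change score does worse than the final score.
- **That the efficacy conclusion will rest on the paired tests.** Nothing says so. The paired tests are planned at the same threshold as the between-arm test, and the misuse is a risk the wording leaves open.
- **That testing at two post-baseline visits inflates the error rate of the primary outcome.** Section 2.4.2 says when scores are recorded. Nowhere does the article say that the arms are tested at each visit, so no familywise error can be charged to the plan.

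It could also be said that covariates are commonly left to an analysis plan. That would answer a silent protocol, but this one names its tests, and the recommendation is to improve the tests it names.

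**Conclusion.** The point holds as a free improvement to a stated method. The between-arm ANOVA is valid but less precise than ANCOVA. At 26 per arm and 0.6 SD, ANCOVA gains 4, 12 or 28 percentage points of power (from unrounded figures) over a final-score ANOVA at correlations of 0.3, 0.5 and 0.7, and about 17, 12 or 6 points over a change-score ANOVA. In every case computed, ANCOVA was at least as powerful as either. These sizes rest on the assumed difference and correlations and on 20% drop-out from 66.

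The criticism of the paired tests needs no assumed effect size, because with the same cream in both arms a within-arm P value does not isolate acupuncture. How often the two tests would disagree does depend on the assumed improvement and ranges from 5% to 48% over the values shown.

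**What to change.** In Section 2.7, make the between-arm comparison the sole efficacy test: an ANCOVA of the total skin lesion score at the end-of-treatment assessment on arm and baseline score, reported as the adjusted mean difference with its 95% CI. Report changes within each arm descriptively, without P values.

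That assessment must first be defined, and the article's schedules do not yet agree. Three two-weekly evaluations starting before treatment fall at weeks 0, 2 and 4, and the cream course is 4 weeks. Acupuncture is 3 courses of 10 sessions on alternate days: 30 sessions, with the last on day 1 + 29 × 2 = 59. Sections 2.3 and 2.4.2 need to be reconciled by the investigators; this point takes no position on which schedule should stand.

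The analysis change itself costs only wording. The baseline score is already collected, the named software fits ANCOVA, and Section 2.9 says recruitment has not started. Whether reconciling the schedules alters data collection depends on how the investigators resolve them.

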### Data management

2.8

Information obtained from the evaluation of each participant will be recorded on a paper printout. The information will then be handwritten on a paper document case report form and entered into an Excel file for future statistical analyses. In accordance with the Personal Information Protection Act, the names of all participants will not be disclosed, and a unique identifier number given during the trial will be used to identify participants. All of the participants will be informed that the clinical data obtained in the trial will be stored in a computer and will be handled with confidentiality. The participants’ written consent will be stored by the principal investigator.

### Ethics

2.9

The study protocol is going to be approved by the ethics committee of the Third People's Hospital of Ningxia. The study will be conducted under the Declaration of Helsinki principles, as well as following the norms of good clinical practice. Recruitment of patients has not started in this study. The study plan will be submitted to the ethics committee of the Third People's Hospital of Ningxia for review. We will not start recruiting participants without the consent of the ethics committee. The protocol of this study has been registered in the Chinese Clinical Trial Registry with the number ChiCTR2000030427.

